#### · *Primary aim*

Evaluate the feasibility and acceptability of the research procedures, including:

Assessing recruitment capability and participant characteristics: Recording the recruitment process, including participant numbers screened, eligible, approached, consented, and excluded after screening; then calculating the relevant rates.Assessing intervention and study procedures’ acceptability and suitability: a) Participants’ evaluation of the intervention and study procedures; b) Whether the rationale for participant dropout is associated with the intervention and study procedures; c) Participants adherence to the intervention including the compliance rate for completion of the entire study, health education, and exercise, respectively; d) Follow-up rate = Number of participants who complete the follow-up stage / Number of participants who complete the six-week exercise intervention.Assessing data collection procedures and outcome measurements: a) Time needed to collect data; b) Experiences of the secondary outcome measures, such as whether they feel fatigued or burdened.Assessing resources and the ability to conduct the study and intervention: a) Duration of time required to complete each step of this study; b) Ability to complete the study within the allotted time; c) Capacity of researchers to collaborate with community healthcare professionals; d) Evaluate researchers’ data organization, management, and analysis ability.Assessing participant responsiveness to intervention: a) Investigate subjective experiences of the participants during the intervention; b) Measure objective outcomes before and after intervention.

#### · *Secondary outcomes*

Table 1 outlines the two types of secondary outcomes that will be evaluated at various points throughout the study. The first category consists of muscle-related outcomes, including muscle strength, muscle mass, and physical performance. The second category includes additional body parameters such as anthropometric indices, nutrition state, perceived knowledge, personal motivation, behavioral skills, and monitoring of behavior change. The questionnaire survey, like MNA-SF, SEMCD-6, and the Self-Management for Chronic Disease Scale, will be conducted after the physical measurements are assessed. The PI will ask participants the questionnaire questions verbally and will record their answers electronically. If participants wish to see the questionnaires, they will be provided with a paper copy. Those measurements will take about 30–40 minutes in total to complete, which will be assessed in an office provided by the community health center.

**Table 1 pone.0303481.t001:** Overview of instruments and time of outcome measures.

MEASURES	INSTRUMENTS	TIMEPOINT					
		T_0_	Intervention			Follow-up	
			T_1_	T_4_	T_7_	T_10_	T_13_
Social-demographic information	Demographics questionnaire (Self-developed)	**X**					
**Primary outcome**							
Feasibility and acceptability	Research record sheet (Self-developed)	**X**	**X**	**X**	**X**	**X**	**X**
**Secondary outcome**							
Handgrip strength	Digital hand-held dynamometer	**X**		**X**	**X**	**X**	**X**
Anthropometric measurements (e.g. weight, height)	Stadiometer + Scale + Plastic tape	**X**		**X**	**X**	**X**	**X**
Body composition (e.g. muscle mass, body fat)	Bioelectrical impedance analyzer device	**X**		**X**	**X**	**X**	**X**
Physical performance	4-Meter Walk Test	**X**		**X**	**X**	**X**	**X**
	Five Times Sit to Stand Test	**X**		**X**	**X**	**X**	**X**
Nutrition state	Mini-Nutritional Assessment Short Form	**X**		**X**	**X**	**X**	**X**
Perceived knowledge	21 true or false quizzes related to sarcopenia (Self-developed)	**X**	**X**	**X**	**X**	**X**	**X**
Personal motivation	Self-efficacy for Managing Chronic Disease 6-item Scale	**X**		**X**	**X**	**X**	**X**
Behavioral skills	Self-management Behavior for Chronic Disease Scale	**X**		**X**	**X**	**X**	**X**
Behavior change monitoring	Exercise diary (Self-developed)	**X**	**X**	**X**	**X**	**X**	**X**
	Exercise Adherence Rating Scale (EARS)	**X**		**X**	**X**	**X**	**X**
	Records of sharing sarcopenia-related information (Self-developed)	**X**	**X**	**X**	**X**	**X**	**X**
	Willingness to formulate habits of regular exercise after study (Self-developed)						**X**
	Records of exposure percentage of exercise and sarcopenia related videos (Self-developed)	**X**	**X**	**X**	**X**	**X**	**X**

Note: T_0_ = baseline; T_1_ = week 1; T_4_ = week 4; T_7_ = week 7; T_10_ = week 10; T_13_ = week 13.

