#### · *Inclusion criteria*

60~69 years oldChinese residents living in the communityHave a smart phone with an internet connection at home, existing users of TikTok or have a willingness to download and use TikTok

Individuals with sarcopenia screening questionnaire: Five-item (strength, walking assistance, rising from a chair, stair-climbing, and falls) combined with calf circumference [SARC-CalF] ≥11 [2,32]

Individuals with possible sarcopenia, as defined by low Grip Strength [M:<28 kg, F:<18kg] in accordance with the 2019 Asian working group consensus on diagnosis criteria for sarcopenia [2]Be able to attend the community health center (at their own expense if travel is required) on six occasions for the duration of the studyInformed consent for screening and research

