### Intervention

Participants will receive the SHEEP intervention strategy [23], which consists of one-week of health education and six-weeks of exercise. Participants will be required to view a total of seven health education videos posted on TikTok in the first week, including the following: 1) What is sarcopenia? 2) What are the common influencing factors in sarcopenia? 3) What are the adverse effects of sarcopenia? 4) What are the manifestations of sarcopenia in daily life? 5) What are the common screening methods for sarcopenia? 6) What are the exercise methods to prevent sarcopenia? 7) What are the nutritional methods to improve sarcopenia? Each video lasts four to six minutes. There is no restriction on the number of views, so participants are allowed to determine the number of videos they watch per day.

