Participants will attend a six-week exercise training course on TikTok following completion of the health education learning. The duration of the exercise is fixed at 30 minutes and comprises four types of exercise: 3-minute warm-up training, 8-minute aerobic training, 16-minute resistance training, and 3-minute flexibility training. The multicomponent exercise training is informed by the evidence-based FaME exercise program (https://laterlifetraining.co.uk/real-life-implementation-of-fame-does-it-work /), OTAGO exercise program (https://www.livestronger.org.nz/assets/Uploads/acc116 2-otago-exercise-manual.pdf), and our previous study on intervention development which involved collaboration from stakeholders (physicians, nurses, physiotherapists, older participants) [23]. The training is delivered through pre-recorded videos on TikTok. The frequency of exercise must be at least 3 times/week, and participants can increase the frequency of training per week based on their own preferences. The overall exercise intensity is moderate. The resistance exercise is performed using two 500ml or 1000ml or 1500ml or 2000ml capacity water-bottles. Participants can start from 500ml or 1000ml, then adding 100-500ml of weight every three weeks. The increase in weight is not fixed and can be adjusted according to preference. When the body feels no burden after completing an exercise session, for instance the body does not heat, sweat or muscles do not appear slightly sore after exercise, we suggest appropriately increasing the weight. These water bottles are all made of plastic. 500ml and 1000ml water bottles are more common in mineral water bottles or juice bottles, while 1500ml and 2000ml water bottles are more common in sports water bottles.

Finally, participants will be followed up weekly over another 6 weeks of exercise. The researcher will help them record their exercise diary and feeling through a short telephone call or text message each week.

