#### · *Behavior change monitoring*

Three aspects of behavior change will be monitored throughout the entire research procedure, including: 1) Exercise adherence during the intervention and follow-up periods will be calculated by completion rate of minimum exercise required in the study. The Exercise Adherence Rating Scale (EARS) is a validated 16-question instrument with a 6-question subscale assessing adherence; the remaining questions measure reasons for adherence/non-adherence. As stated in the study [46], EARS is a valid and reliable tool that allows for the assessment of compliance with suggested home exercise. The six items comprise a unidimensional scale that exhibited favorable measurement features, including satisfactory internal consistency and strong test-retest reliability. 2) Percentage of participants who actively view and share sarcopenia-related information to others. 3) Percentage of participants willing to formulate habits of regular exercise to prevent sarcopenia at the end of the current study. 4) Exposure percentage of exercise and sarcopenia-related videos = Number of exercise and sarcopenia related videos viewed / Twenty videos. TikTok can push videos to users that they are interested in based on big data algorithms; therefore, if participants begin to view more videos about exercises and sarcopenia after health education in our research, TikTok will capture these changes in their viewing habits and push more videos about exercises and sarcopenia to them. Then, researchers can record the number of exercise and sarcopenia-related videos when every twenty videos are viewed on participants’ TikTok and observe the exposure percentage of exercise and sarcopenia-related videos to determine if participants’ video-scrolling behavior changes.

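### EARS is scheduled at baseline before any study exercise has been suggested, and later TikTok exposure values can rise from required viewing, so neither change from T0 can be read as planned

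*Protocol article*

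**What the plan says.** **EARS.** Table 1 lists the "Exercise Adherence Rating Scale (EARS") under behavior change monitoring, with marks at T0, T4, T7, T10 and T13 and none at T1. The note to the table reads "T_0_ = baseline; T_1_ = week 1; T_4_ = week 4". The section Behavior change monitoring states that "EARS is a valid and reliable tool that allows for the assessment of compliance with suggested home exercise", and also that "Exercise adherence during the intervention and follow-up periods will be calculated by completion rate of minimum exercise required in the study". On timing, the Intervention section says: "Participants will attend a six-week exercise training course on TikTok following completion of the health education learning".

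**TikTok exposure.** The same monitoring section defines an exposure percentage: exercise and sarcopenia videos viewed, divided by twenty. Table 1 records it at all six time points. The stated reasoning is that "if participants begin to view more videos about exercises and sarcopenia after health education in our research, TikTok will capture these changes" and then push more such videos, so that the percentage shows whether scrolling behavior has changed. The Intervention section says that "Participants will be required to view a total of seven health education videos posted on TikTok in the first week" and delivers the exercise through pre-recorded TikTok videos at least three times a week for six weeks. The inclusion criteria admit "existing users of TikTok or have a willingness to download and use TikTok".

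**Analysis.** The Outcomes section places study adherence among the measures compared at baseline, week 7 and the end of follow-up in order to judge potential efficacy. Data collection and analysis applies 95% confidence intervals to before-after differences in the secondary outcomes.

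**The concern.** A change from baseline means something only if the baseline and the later values measure the same thing. For EARS they do not: at T0 the participant has been given no study exercise to adhere to. For exposure, the T0 value is taken before any required viewing, but the later values mix two sources: what participants choose to watch, and what the study obliges them to watch together with what TikTok then serves in response. A single arm offers no comparison group to separate the two, and a larger sample would not remove the mixture.

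The Discussion presents the study as the first to observe the effect of a social-media intervention on awareness and behavior change in this field. The Outcomes section intends the measures to help choose a primary outcome and supply parameters for a later RCT. A change that reflects the schedule or the platform could mislead either use.

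**Working it through.** The plan gives no figure to reproduce here. The check sets the passages side by side, with a little arithmetic for scale.

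**1. Does EARS have a referent at each scheduled visit?**

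| Visit | Study stage | Exercise suggested by the study? | EARS marked? |
|---|---|---|---|
| T0 | before education | no | yes |
| T1 | education week | no, the course follows the education | no |
| T4, T7 | exercise course | yes | yes |
| T10, T13 | follow-up, in which the Intervention section expects a further six weeks of exercise | yes | yes |

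T0 is the only marked visit without a referent. The blank at T1 fits the scale's meaning, while the mark at T0 does not. The sentence on completion-rate adherence likewise covers only the intervention and follow-up. Pre-study exercise cannot simply be taken as the referent: people already doing regular moderate exercise of 150 minutes or more a week are excluded, and self-chosen activity has not been suggested by anyone in the study. Five marked visits give four possible changes from T0 (to T4, T7, T10 and T13), and all four use the T0 score.

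**2. Is a baseline comparison planned?** Yes. The Outcomes section names study adherence in a comparison that includes baseline. The section Secondary outcomes includes behavior change monitoring, and the analysis section applies before-after intervals to secondary outcomes.

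**3. By what routes can exposure rise without voluntary change?**

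- *Direct counting.* The formula is related videos / 20, and it does not say that study videos are left out. Each one counted adds 1/20 = 5 percentage points. The article does not say how many would fall in a window, so as an assumed range: 0/20 = 0, 3/20 = 15 and 7/20 = 35 points.
- *Algorithm feedback.* The article says that TikTok pushes what is viewed. Required viewing is seven education videos in week 1 and at least 3 × 6 = 18 exercise sessions by week 7. This route stays open even if no study video is counted, and the documents give no basis for estimating its size.

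**4. Is the T0 exposure value sound?** It precedes all required viewing. For an existing TikTok user it reflects an established feed and is a genuine baseline. For someone who downloads TikTok for the study there is no viewing history, so the value says little about habits. The article does not say how many participants will be new users.

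**The case against.** Several points on the other side have force.

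- *Exposure has a real baseline.* A reader might infer that both measures lack a valid one. The documents do not support that: T0 exposure precedes the intervention and is valid for existing users. The weakness lies mainly in the later values. This objection stands.
- *A rise is not assured.* A reader might infer that both measures must show behavior change whatever participants do. For EARS, a T0 score without a referent leaves even the direction of change undefined, and later scores reflect whether the exercise was done, which is itself the behavior. For exposure, the effect of required viewing is plausible on the article's own account but unquantified. The point is that the measures can mislead, not that they will.
- *Counts and sampling noise do not establish bias.* It is tempting to set the required viewing accumulated over seven weeks against the 20-video window. The units differ, and the article does not equate one session with one video play. The sampling error of a single 20-video window is noise within one person and does not bear on bias.
- *The measure may concern the feed only.* The wording about pushed videos and scrolling suggests this, and a condensed article may leave the recording rule to the full protocol. That softens the direct-counting route. It does not touch the feedback route, nor the stated reading of the percentage as scrolling change.
- *The impact is limited.* Both are secondary monitoring items in a feasibility study. The analysis section's before-after examples are grip strength, muscle mass and body fat. Completion-rate adherence does not rely on EARS at T0, and the monitoring section separately records active viewing and sharing. All this stands and limits the weight of the point, but the Outcomes section still puts adherence into a baseline comparison.

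**Conclusion.** The point holds in two parts of unequal strength.

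**EARS:** the T0 mark conflicts with the article's own description of the scale and with its own timetable. All four changes from T0 are uninterpretable. This rests on the text alone and needs no numerical assumption. Scores at T4 to T13 are unaffected.

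**Exposure:** the post-baseline percentage cannot by itself show a voluntary change in scrolling, because required viewing can raise it. This rests on the article's own account of how TikTok responds to viewing. The size is unknown; the 5 points per counted study video is arithmetic, and the number counted is an assumption. The baseline is valid for existing users and uninformative only for new ones.

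Neither part affects the primary feasibility aim. Both are worth correcting because the measures feed the behavior-change claim and the planning of the RCT.

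**What to change.** 1. Delete the T0 mark for EARS in Table 1. Summarise EARS descriptively at T4, T7, T10 and T13, with no change from baseline.
2. State that study videos are excluded from the 20-video count.
3. Record whether each participant entered as an existing or a new TikTok user. Report exposure change from T0 for existing users only, and give new users' values descriptively with no baseline. T1 should not serve as their substitute baseline, because it follows the seven required videos.
4. Interpret the percentage as algorithmic exposure that includes the effect of mandated viewing, not as proof of voluntary behavior change. This is needed even after step 2, since leaving study videos out of the count does not undo their effect on the feed.

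The cost is one table edit, one added definition and one recorded item. There is no extra visit, and the baseline assessment is slightly shorter. The real downside is that exposure change rests on fewer participants, by a number the article does not allow one to estimate.

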#### · *Handgrip strength*

Handgrip strength (kg) will be measured with a digital hand-held dynamometer (EH101, Xiangshan Inc, Guangdong, China). In a seated position with the elbow flexed at 90 degrees, the shoulder attached to the thorax, and the wrist in a neutral position (0 degrees), the maximal grip strength is measured. The measurements are taken three times on each side (left and right), with a 30-second interval between each assessment [35].

#### · *Anthropometric measurements*

Height will be measured to the nearest 0.1 cm using a stadiometer, and weight will be measured to the nearest 0.1 kg using a scale. Calf circumference and abdominal circumference will also be measured using a tape measure for both legs and the navel, respectively, to the nearest 0.1 cm.

#### · *Body composition*

Body composition measurement will be conducted using a multi-frequency bioelectrical impedance analyzer device (InBody S10; Biospace, Seoul, Korea) according to the manufacturer’s guidelines. BIA calculates body composition by comparing the conductivity of various tissues based on their distinct biological properties. As a cell approaches an ideal spherical shape, its conductivity decreases, as it is proportional to water content and, more specifically, electrolytes. Since adipose tissue is composed of round-shaped cells and contains relatively little water in comparison to other tissues such as muscle, the conductivity of the body will decrease as body fat increases. In order to conduct a multi-segment frequency analysis, electrodes are set at six precise tactile points of the body. Using six different frequencies (1 kHz, 5 kHz, 50 kHz, 250 kHz, 500 kHz, 1000 kHz), more than 30 impedance measurements are obtained from the right and left arms, trunk, and right and left legs [36]. The following body index parameters will be chosen for analysis in this study: skeletal muscle mass (kg), skeletal mass index (kg/m^2^), upper-extremity skeletal muscle mass (kg), lower-extremity skeletal muscle mass (kg), trunk skeletal muscle mass (kg), body fat (kg), body fat percentage (%), body mass index (kg/m^2^), protein (kg), and bone mineral (kg).

#### · *Physical performance*

Physical performance will be measured by using a 4-Meter Walk Test (4- MWT, m/s) and a Five Times Sit to Stand Test (FTSST, s).

First, the participants’ self-selected walking speed will be measured using a 4-MWT (with 2m for acceleration/deceleration) [37]. At the beginning and end of the timed walkway, space will be provided for participants to accelerate and decelerate outside of the data collection area to reduce gait variability introduced during these phases. Participants will be instructed to "walk at a comfortable, normal pace" until reaching the end of the marked path; and each participant must accomplish three consecutive measurements. A researcher will measure walking time using a stopwatch (ZSD-013, China), starting it when the participant’s lead leg crosses the first marker and stopping it when it crosses the second marker. To prevent interobserver variation, all stopwatch measures will be conducted by the same researcher. Throughout the testing session, participants will be provided with breaks as required.

Second, participants will sit on an armless chair with a 43 cm (cm) seat height to commence the FTSST [38]. Each participant will be instructed to sit with their back against the chair’s backrest and their arms crossed over their torso. The researcher will then demonstrate the proper technique for performing the test, including coming to a full stand, which is defined as an upright trunk with extended hips and knees. A researcher will measure the time using a stopwatch (ZSD-013, China). Timing will commence when the researcher says "go" and end when the participant’s glutes touch the seat after the fifth stand [39]. The participants must stand and sit five times "as quickly as possible" and without physical assistance. The researcher will not use encouraging words or body language to encourage participants to speed up their performance.

#### · *Nutritional status*

The Mini-Nutritional Assessment Short Form (MNA-SF), a valid nutritional screening instrument applicable to geriatric health care professionals, will be used to evaluate nutritional status [40]. The MNA-SF consists of six items and one anthropometric measurement (either body mass index [BMI] or calf circumference [CC]) to identify individuals at risk of malnutrition. Maximum MNA-SF score is 14, with scores≤11 indicating possible malnutrition and scores ≥12 confirming normal nutritional status [41]. MNA-SF, having fewer items than Full-MNA, requires less measuring time while achieving similar predictive power as Full-MNA [40,42].

